## Abstract

**Objective:**

Postpartum stress urinary incontinence (PSUI) is a common condition among women after childbirth. While acupuncture is a common clinical treatment for PSUI, high-quality clinical evidence supporting its effectiveness is currently lacking. This study aims to preliminarily evaluate the efficacy and safety of acupuncture for early postpartum stress urinary incontinence, providing reference data for sample size calculation and protocol feasibility in formal trials.

**Design and methods:**

This is a randomized controlled trial. Seventy-two PSUI patients between 42 days and 1 year postpartum will be randomly assigned in a 1:1 ratio to either the acupuncture group (n = 36) or the sham acupuncture group (n = 36). Both groups will receive acupuncture treatments three times per week for two weeks. Both groups will receive identical education regarding pelvic floor muscle training. The primary outcomes are changes in urine leakage volume measured by 1-hour pad test at week 2 of treatment and week 6 of follow-up compared to baseline (week -1), and the proportion of patients achieving at least 50% reduction in urine leakage volume at week 2 compared to baseline. Secondary outcomes include 72-hour bladder diary, The International Consultation on Incontinence Questionnaire-Short Form (ICIQ-SF), Incontinence Quality of Life questionnaire (I-QOL), and pelvic floor muscle strength assessment.

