Traditional Chinese medicine offers various SUI treatments, with acupuncture showing the most promising results. A 504-patient RCT found electroacupuncture significantly reduced urine leakage and improved quality of life in middle-aged/elderly women, with clear clinical efficacy and safety [9]. PSUI differs from general SUI, as PSUI is caused by pelvic floor and supporting structure damage from pregnancy/childbirth, while SUI often results from pelvic organ prolapse or muscle weakness. Therefore, the symptoms and treatments for PSUI and SUI are not entirely identical. Previous research has explored acupuncture for PSUI, but evidence on its efficacy is limited [10–12]. High-quality randomized controlled trials are needed to thoroughly evaluate the effectiveness and safety of acupuncture for PSUI treatment. Positive findings could provide a new clinical approach for PSUI while bolstering Traditional Chinese Medicine’s application in modern medicine.

This pilot trial aims to provide evidence that acupuncture has therapeutic effects on PSUI beyond placebo. Prior studies lack sham-controlled acupuncture as a comparator for PSUI [10–12]. To our knowledge, this will be the first acupuncture trial using non-acupoint, shallow, and non-deqi needling as a sham control to rigorously evaluate acupuncture’s efficacy for PSUI. If the true acupuncture group shows superior results, it would preliminarily confirm acupuncture’s therapeutic benefits and inform future formal trials.

The primary objective of this trial is to verify the feasibility of the protocol, defined as meeting the following criteria: (1) dropout rate ≤20%; (2) compliance rate ≥80%; (3) data completeness ≥90%; (4) adverse event rate <5%, with no intervention-related serious adverse events. The secondary objective is to collect preliminary parameters for sample size calculation, including: (1) mean between-group difference in the 1-hour pad test; (2) standard deviation of outcome measurements; (3) estimated effect size (Cohen’s d).

Two hypotheses are proposed: (1) Acupuncture can reduce urine leakage volume in patients with PSUI; (2) Acupuncture is a safe intervention for treating PSUI.

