### Outcomes

#### Primary outcomes.

The primary outcome in this study is the change in the 1-hour pad test, which is a medical test recommended by the International Continence Society (ICS). The measurement method primarily involves instructing patients to complete a series of movements, and measuring the change in pad weight to determine the amount of urine leakage during the test process. The entire testing process is supervised by researchers, while the placement and removal of the pad is performed by the patients themselves. The 1-hour pad test can objectively and accurately measure the patient’s urine leakage volume and effectively observe changes in leakage volume after treatment, making it an objective and accurate indicator for observing therapeutic efficacy.

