### Statistical analysis

Statistical analysis will be performed using SPSS software version 26.0. Measurement data will be presented as means and standard deviations (SD) or medians and interquartile ranges (IQR), as appropriate. Counting data will be expressed as percentages.

Efficacy evaluation will adhere to the intention-to-treat (ITT) principle, including all patients who have received at least one treatment. For the primary outcome (1-hour pad test) and secondary outcomes (72-hour bladder diary, ICIQ-SF scores, I-QOL scores, pelvic floor muscle strength test results, and patient self-evaluation of efficacy), a mixed-effects model will be employed to account for the characteristics of repeated measures data. The model will include group, time points, and their interaction as fixed effects, with participants treated as random effects. Baseline values will be incorporated as covariates.

Missing data will be handled using multiple imputation. Five datasets will be generated based on age, sex, body mass index (BMI), baseline characteristics, and outcome values at other time points for analysis. Two sensitivity analyses will be performed for the primary outcome (1-hour pad test): (1) an analysis of the dataset without imputation to assess potential bias introduced by imputation and (2) an analysis of the per-protocol (PP) set to evaluate the impact of adherence. The PP set is defined as participants who completed at least 80% of the planned treatments without significant protocol violations (i.e., at least five treatments in both the acupuncture and sham acupuncture groups).

Safety analysis will include all participants who received at least one treatment. AE rates will be described using counts and percentages. Between-group comparisons will be conducted using the chi-square test when the expected frequency requirements are met; otherwise, Fisher’s exact test will be used. All statistical analyses will be two-tailed, with a significance level of *P *< 0.05 considered statistically significant.

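### The article gives three different answers to what is primary (two pad-test changes plus a responder rate, the pad test alone, or feasibility), and the responder rate has no analysis

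*Protocol article*

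**What the plan says.** Four parts of the article bear on this.

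- **Abstract, Design and methods.** "The primary outcomes are changes in urine leakage volume measured by 1-hour pad test at week 2 of treatment and week 6 of follow-up", each against baseline, together with "the proportion of patients achieving at least 50% reduction in urine leakage volume at week 2 compared to baseline". That is two endpoints, one of them at two time points, so three comparisons.
- **Outcomes, Primary outcomes.** "The primary outcome in this study is the change in the 1-hour pad test". No time point is given and no responder endpoint appears. The Statistical analysis section and the Discussion also name only the 1-hour pad test as primary.
- **Introduction, objectives.** "The primary objective of this trial is to verify the feasibility of the protocol, defined as meeting the following criteria": dropout no more than 20%, compliance at least 80%, data completeness at least 90%, and adverse events under 5% with no serious event attributable to the intervention. Then: "The secondary objective is to collect preliminary parameters for sample size calculation". An efficacy hypothesis stands beside these: "Acupuncture can reduce urine leakage volume in patients with PSUI". The Introduction adds that superior results would count as preliminary confirmation of benefit, without naming an outcome or a week.
- **Statistical analysis.** One mixed model serves the pad test and the secondary outcomes: "The model will include group, time points, and their interaction as fixed effects, with participants treated as random effects", with baseline as covariate. A two-sided 0.05 level covers all analyses. Chi-square and Fisher tests are named only for safety.

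**The concern.** A reader of the eventual report should be able to tell from the protocol which result answers the primary question. Here that depends on the section consulted. By the abstract, there are three efficacy comparisons. By the Methods, there is one pad-test outcome. By the objectives, the primary question is not efficacy at all.

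Two consequences follow. First, the result labelled primary could be selected once the data are seen, and whichever comparison reaches 0.05 could be defended from some part of the text. The comparisons are not interchangeable: an effect that fades after treatment could show at week 2 and not at week 6. Secondly, the declared primary objective has no designated primary outcome, while an outcome that the abstract calls primary has no method of analysis.

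**Working it through.** **1. The places side by side.**

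| Item | Abstract | Introduction | Outcomes | Statistical analysis |
|---|---|---|---|---|
| Pad-test change, week 2 | primary | not dated | pad test primary, no week | pad test primary, no week singled out |
| Pad-test change, week 6 | primary | not dated | as above | as above |
| Responder proportion, week 2 | primary | absent | absent | absent |
| Dropout, compliance, completeness | absent | primary objective | absent | no rate analysis stated |
| Adverse event rate | absent | primary objective | absent (separate safety section) | counts, percentages, chi-square or Fisher |

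The per-protocol definition uses an 80% threshold per participant (3 × 2 = 6 sessions; 0.8 × 6 = 4.8, so five). That defines a sensitivity set; it does not plan an analysis of the compliance rate.

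**2. Does the model reach the responder proportion?** The mixed model takes pad weight as a continuous response, and its group and interaction terms describe differences in mean leakage. A 50% reduction is a binary outcome per woman, so its between-group difference is not a term or contrast of that model.

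**3. Does the sample size depend on the choice?** Inputs from the Sample size section: 30 per group as a pilot rule, 20% for dropout. 30 × 1.2 = 36 per group and 2 × 36 = 72, which reproduces the stated figures. No alpha, power, effect size or outcome enters, so N does not change with the outcome called primary.

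**4. Size of the error if any one comparison counts.** This success rule is an assumption; the article does not state one. Level per test: 0.05, two-sided.

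- Independent tests: 1 − (1 − 0.05)³ = 1 − 0.857 = 0.143.
- Equicorrelated normal test statistics, by simulation, correlations assumed:

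| Correlation | Chance that at least one of three is significant |
|---|---|
| 0 | 0.143 |
| 0.3 | 0.136 |
| 0.5 | 0.126 |
| 0.7 | 0.109 |
| 0.9 | 0.084 |
| 1 | 0.050 |

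- Null simulation, 36 per arm, assumed log-normal pad weights with between-visit correlation 0.3 to 0.85, baseline-adjusted comparison at each week, and a two-proportion test for responders: 0.123 to 0.132 for all three, and 0.092 to 0.098 for the two pad-test weeks alone. The week-2 mean and responder statistics correlated at 0.64 to 0.74 in absolute value, and the two pad-test weeks at 0.23 to 0.46.

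**5. After the change.** One designated contrast: 0.05. If all three stayed primary with any one sufficient, Bonferroni gives 0.05 / 3 = 0.0167 each, and 1 − (1 − 0.0167)³ = 0.049 under independence.

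**The case against.** The strongest reply is that this is a condensed article on a pilot trial. The full protocol and any statistical analysis plan are not shown, and the choice of contrast and any multiplicity rule commonly sit there. That stands. A reader might infer that no multiplicity rule exists; the article supports only that it prints none, and that alone is no finding. Nor does listing group, time and interaction as fixed effects make each a separate primary test.

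Other parts of the reply also stand:

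- The 14.3% figure needs independence, which cannot hold. Week-2 change and week-2 responder status come from the same pad weights, and week 6 is a repeat in the same women against the same baseline. All the error figures also need the any-one-counts rule.
- The Outcomes section omits the weeks; it does not contradict the abstract's weeks 2 and 6. The schedule figure is not shown.
- It would be too strong to say that no feasibility measure is analysed. Adverse event rates are. Dropout is defined under Shedding criteria, and comparing an observed rate with a fixed threshold needs no elaborate model.
- The article calls its evidence preliminary, concedes that the sample may not support definitive conclusions, and leaves confirmation to later trials.

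What the reply does not remove is the disagreement within the article. An analysis plan elaborates a primary outcome; it does not explain why two sections of the same publication define it differently, or why the primary objective is matched by no primary outcome.

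**Conclusion.** The point holds as an internal contradiction about what is primary. The responder proportion is primary in the abstract and absent from the Methods. Feasibility is the primary objective, yet none of its criteria is listed as an outcome and only adverse event rates have a stated analysis.

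The numerical consequence is conditional: roughly 11% to 13% in place of 5% if any of three comparisons were taken as success, at assumed correlations of 0.5 to 0.7, with 14.3% as the upper figure under independence. A reader might go further and say that the two descriptions will give opposite verdicts, or that the trial's error rate is 14.3%. The article contains no verdict rule, so neither follows.

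Severity: should-fix. This is a pilot whose sample size rests on a rule of thumb, and no power statement is affected. The harm is an efficacy result labelled primary after the fact and then over-read.

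**What to change.** Align the abstract, the Introduction's objectives, the Outcomes section and the Statistical analysis section:

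1. Make the four feasibility criteria the primary outcomes, matching the stated objective, each reported with an exact 95% confidence interval beside its threshold.
2. Name one dated between-group pad-test contrast from the mixed model as the lead efficacy estimate. Week 2, the end of treatment, is one reasonable choice. The documents do not rank it above week 6, so the investigators should choose and say why.
3. Make the other pad-test time point and the responder proportion secondary. Report the responder proportion as a between-group risk difference with a 95% confidence interval.

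If the investigators prefer to keep all three efficacy comparisons primary, they should state the success rule and a matching multiplicity adjustment.

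This must be done before unblinding, and preferably before any comparison by coded group. The Blinding section places unblinding after the analysis, and A/B labels do not hide which comparison has the smallest p-value.

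The cost is wording: no new data or participants and no change in sample size. The downside is that two outcomes lose primary status.

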**Discussion:**

The results of this study will provide preliminary evidence on the efficacy and safety of acupuncture for PSUI, offering reference data for sample size calculation and protocol feasibility in formal trials, ultimately providing more treatment options for PSUI patients.

**Trial registration:**

ITMCTR2024000290.

## Introduction

Stress urinary incontinence (SUI) is a common condition in women characterized by involuntary urine leakage during sudden increases in abdominal pressure, such as coughing, laughing, sneezing, or lifting heavy objects, despite having no urinary symptoms under normal circumstances [1]. As a crucial public health issue globally, urinary incontinence (UI) affects the physical and mental well-being of approximately 45% of adult women, with stress urinary incontinence (SUI) being the predominant subtype, accounting for over half of UI cases. In the United States, the prevalence of UI from 2005 to 2016 was 53%, with 26% of women suffering from SUI [2]. In mainland China, the prevalence of SUI among adult women is 24.5% [3].SUI patients often experience incontinence in public settings, leading to body odor issues that can trigger anxiety, fear, and depression in social and work situations. Although SUI is not life-threatening, it significantly impacts patients’ daily lives, work, and social activities. Based on these considerations, World Health Organization (WHO) has identified SUI as a social issue affecting global women’s quality of life and mental health [4].

Postpartum stress urinary incontinence (PSUI) is a common condition in women after pregnancy and childbirth. Studies show the incidence of postpartum urinary incontinence (PPUI) is around 26% [5], with stress UI (54%) being the most prevalent type, affecting first-time and experienced mothers similarly [6].

For mild to moderate PSUI, conservative treatments are typically used, while severe cases are often recommended for surgery. International guidelines recommend lifestyle modifications, behavioral therapy, pelvic floor muscle training (PFMT), and functional electrical stimulation as standard conservative therapies for mild to moderate female stress UI. PFMT is the first-line conservative treatment, with 30–60% efficacy, but requires at least 3 months of adherence to achieve maximum benefits [7]. However, many patients struggle to adhere to PFMT. Biofeedback combined with electrical stimulation is a common clinical approach, but its long-term efficacy is inconsistent, and the treatment is costly for patients [8]. Existing PSUI treatments have limitations, highlighting the need for alternative or supplementary therapies.

Traditional Chinese medicine offers various SUI treatments, with acupuncture showing the most promising results. A 504-patient RCT found electroacupuncture significantly reduced urine leakage and improved quality of life in middle-aged/elderly women, with clear clinical efficacy and safety [9]. PSUI differs from general SUI, as PSUI is caused by pelvic floor and supporting structure damage from pregnancy/childbirth, while SUI often results from pelvic organ prolapse or muscle weakness. Therefore, the symptoms and treatments for PSUI and SUI are not entirely identical. Previous research has explored acupuncture for PSUI, but evidence on its efficacy is limited [10–12]. High-quality randomized controlled trials are needed to thoroughly evaluate the effectiveness and safety of acupuncture for PSUI treatment. Positive findings could provide a new clinical approach for PSUI while bolstering Traditional Chinese Medicine’s application in modern medicine.

This pilot trial aims to provide evidence that acupuncture has therapeutic effects on PSUI beyond placebo. Prior studies lack sham-controlled acupuncture as a comparator for PSUI [10–12]. To our knowledge, this will be the first acupuncture trial using non-acupoint, shallow, and non-deqi needling as a sham control to rigorously evaluate acupuncture’s efficacy for PSUI. If the true acupuncture group shows superior results, it would preliminarily confirm acupuncture’s therapeutic benefits and inform future formal trials.

The primary objective of this trial is to verify the feasibility of the protocol, defined as meeting the following criteria: (1) dropout rate ≤20%; (2) compliance rate ≥80%; (3) data completeness ≥90%; (4) adverse event rate <5%, with no intervention-related serious adverse events. The secondary objective is to collect preliminary parameters for sample size calculation, including: (1) mean between-group difference in the 1-hour pad test; (2) standard deviation of outcome measurements; (3) estimated effect size (Cohen’s d).

Two hypotheses are proposed: (1) Acupuncture can reduce urine leakage volume in patients with PSUI; (2) Acupuncture is a safe intervention for treating PSUI.

## Methods

### Study design

This is a pragmatic, single-center, two-arm, randomized controlled trial conducted in China. A total of 72 postpartum women with stress urinary incontinence will be randomly allocated in a 1:1 ratio to an acupuncture group and a sham acupuncture group. The trial duration is six weeks, including a two-week treatment period and a four-week follow-up. The study protocol has been approved by the Ethics Committee of Beijing University of Chinese Medicine Third Affiliated Hospital (Approval No. BZYSY-2024KYKTPJ-23) and registered on the International Traditional Medicine Clinical Trial Registry platform (ITMCTR, [http://itmctr.ccebtcm.org.cn/]) with registration number ITMCTR2024000290 (Date: August 24, 2024, version 4.0). The trial design adheres to the Standards for Reporting Interventions in Clinical Trials of Acupuncture (STRICTA) [13] and the Standard Protocol Items: Recommendations for Interventional Trials (SPIRIT) guidelines [14]. Fig 1 illustrates the SPIRIT schedule, and S1 File shows the SPIRIT checklist. Fig 2 illustrates the flow chart of this trial.

**Fig 1 pone.0324384.g001:**
[figure not shown]
SPIRIT schedule. Enrollment, Intervention, and Assessment Schedule. PSUI, Postpartum Stress Urinary Incontinence; ICIQ-SF, The International Consultation on Incontinence Questionnaire-Short Form; I-QOL, Incontinence Quality of Life; PF Strength, Pelvic Floor Strength Assessment.

**Fig 2 pone.0324384.g002:**
[figure not shown]
The flow chart of this trial.

### Study site

Recruitment, intervention and follow up will be conducted at Beijing University of Chinese Medicine Third Affiliated Hospital. Following randomization, patients will be allotted to the respective group. Recruitment will take place on outpatient departments, with intervention and follow up occurring in dedicated rooms within the hospitals.

### Participants

#### Inclusion criteria.

Patients will be eligible if they meet the following criteria:

(1)Aged between 20 and 40 years;(2)Within 42 days to 1 year postpartum;(3)Experience urinary leakage during activities such as coughing, sneezing, laughing, or physical exertion, which ceases when the activity stops, occurring ≥1 time in the past three months;(4)Demonstrate an increase in pad weight of more than 1 g but less than 50 g during a 1-hour pad test;(5)Diagnosed with mild to moderate SUI based on the Ingelman-Sundberg classification;(6)Voluntarily agree to participate in the study and sign the informed consent form.

Diagnosis and Ingelman-Sundberg grading will be conducted by a urologist.

#### Exclusion criteria.

Patients will be ineligible if meet any of the following points:

(1)Multiple gestation pregnancy;(2)Pre-pregnancy urinary incontinence symptoms;(3)Urinary frequency and urgency symptoms;(4)Symptoms of urinary tract infection;(5)Incomplete lochia discharge postpartum or presence of intrauterine retention;(6)Concurrent uterine or other gynecological diseases;(7)History of severe pregnancy complications, including: macrosomia, prolonged second stage of labor, placenta previa, threatened preterm labor and gestational hypertension;(8)Previous indications for cesarean section or contraindications to vaginal delivery;(9)Previous urinary incontinence surgery or pelvic floor surgery;(10)Pelvic organ prolapse greater than grade 2;(11)Overactive bladder syndrome or urinary system tumors;(12)Detrusor muscle weakness;(13)Specific treatment for SUI within the past month or use of medications that may affect bladder function;(14)Severe conditions including: cardiovascular disease, cerebral disease, hepatic disease, renal disease, psychiatric disorders, diabetes mellitus, multiple system atrophy, cauda equina injury and spinal cord injury;(15)Presence of cardiac pacemaker, metal allergy, or severe needle phobia;(16)Participation in other clinical trials within the past 3 months.

